### Statistical analysis plan

Baseline demographic, psychosocial and clinical characteristics of participants will be summarised and compared for differences between the intervention and usual care groups. Characteristics of participants who complete and those who withdraw will be compared.

The analysis of the primary outcome (HbA1c) will be assessed using linear regression; secondary outcomes measures will be assessed using either linear regression (continuous outcomes) or logistic regression (binary outcomes). To adjust for potential between-group imbalance, the baseline score of the outcome of interest will be included as a covariate in models. Site allocation will also be included in models as a covariate.

All analyses will be conducted on an intention-to-treat basis. Statistical significance will be based on two-tailed tests, with *P* <0.05 considered significant.

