#### Quantitative study data

Figure 
2 displays the study procedure. Quantitative data collection will include: (1) clinical data extracted from the diabetes clinics’ databases; and (2) patient-reported outcomes collected via patient surveys. These data will be collected at baseline, 6 and 12 months. Clinical data will be extracted every 6 months from the clinics’ databases by a research project officer. General practice records will be relied on for missing clinical data. The surveys will be distributed to patients before they attend their medical appointment by the DNE at each site. All quantitative data will be stored centrally at the university research office in a purpose-designed password-protected web-based database.

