#### Clinical indicators

The primary endpoint is glycaemic control as measured by the mean change in HbA1c.

The other main clinical indicators include: blood pressure; serum cholesterol; high-density lipoprotein (HDL); low-density lipoprotein (LDL); triglycerides; serum creatinine; and estimated glomerular filtration rate (eGFR). Medications, diabetes complications, smoking status and body mass index will be recorded. In addition, health services use information, date of discharge from clinic if applicable and allied health referrals will be collected.

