### Sample size and power calculation

Sample size is based on the primary endpoint of HbA1c using an alpha = 0.05 and power = 80%. Based on findings from the pilot study, the sample size calculation used a pooled standard deviation in HbA1c of 1.7%. The non-inferiority margin is -0.4% and the true difference between the groups in HbA1c at 12 months is predicted to be 0.1%
[26]. A randomisation ratio of 3:1 (intervention to usual) has been chosen so that the clinics at the intervention sites maintain reasonable and sustainable capacity
[16]. Based on the above assumptions and adding a level of attrition of 20% between baseline and 12-month follow-up in both groups, the total sample size is estimated at 456.

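### The stated primary regression gives the 6-month HbA1c no role and, taken literally, uses only patients with a 12-month value, although 20% attrition is expected and the analysis is called intention-to-treat

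*Protocol article*

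**What the plan says.** All references are to the protocol article.

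- **Model.** Statistical analysis plan: "The analysis of the primary outcome (HbA1c) will be assessed using linear regression". On covariates, "the baseline score of the outcome of interest will be included as a covariate in models"; site is added. No time point is named here.
- **Population.** Same section: "All analyses will be conducted on an intention-to-treat basis". Completers and withdrawals are to be compared on their characteristics, which is descriptive and does not alter the estimate.
- **Endpoint.** Clinical indicators: "The primary endpoint is glycaemic control as measured by the mean change in HbA1c", again with no time point. Sample size and power calculation supplies one: "the true difference between the groups in HbA1c at 12 months is predicted to be 0.1" (per cent).
- **Schedule.** Quantitative study data: "These data will be collected at baseline, 6 and 12 months". The same paragraph names general practice records as the back-up source for clinical data that are missing.
- **Expected loss.** The total of 456 was reached after "adding a level of attrition of 20% between baseline and 12-month follow-up in both groups".

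**The concern.** A linear regression of 12-month HbA1c on arm, baseline and site can use a patient only if the 12-month value exists or has been filled in. The article expects a fifth of patients to be lost by then, gives the 6-month measurement no part in the model, and still describes the analysis as intention-to-treat. These statements fit together poorly.

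Such a regression is unbiased if, within arm and given the covariates, having a 12-month value is unrelated to what that value would have been. There is a reason to doubt this. The Intervention section describes discharge to the usual GP once glycaemic, blood pressure and lipid targets are met. The Usual care section gives no matching rule and leaves follow-up to the treating specialist. Since clinical data come mainly from the clinics' databases, availability of a 12-month value could depend on interim control, and differently in the two arms. The 6-month HbA1c is the measurement that could correct for this. In a non-inferiority trial with a margin of 0.4, a shift of 0.1 matters.

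**Working it through.** **1. The plan's own figure.** Inputs from the sample size section: SD 1.7, margin 0.4, predicted difference 0.1, power 80%, ratio 3:1. Taking the 0.1 as favouring the intervention (distance 0.5) and one-sided alpha 0.05:

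- control arm = (4/3) × [1.7 × (1.645 + 0.842) / 0.5]² = 95.3
- with 95 controls the total is 4 × 95 = 380, and 380 × 1.2 = 456, as stated.

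**2. Patients left.** 456 × 0.20 ≈ 91 lost and 456 × 0.80 ≈ 365 observed. Power for 365 at one-sided 0.05 is 78.5%.

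**3. Precision from using the 6-month value.** Let ρ be the correlation of 6- and 12-month HbA1c given baseline, and m the proportion of all patients who lack a 12-month value but have a 6-month one. The effective sample size is

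N_eff = 456 × (0.8 + m) / [1 + (m/0.8)(1 − ρ²)].

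The article gives no correlations. Assume 0.5 (baseline with 6 months), 0.5 (baseline with 12 months) and 0.7 (6 with 12 months). Then ρ = (0.7 − 0.25)/0.75 = 0.6.

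| Dropouts with a 6-month value | N_eff | SE relative to 365 complete cases |
|---|---|---|
| All (m = 0.20) | 393 | √(364.8/393.1) = 0.963 |
| Half (m = 0.10) | 380 | √(364.8/380.0) = 0.980 |

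Simulation agrees: the SE is about 2 to 5% smaller. Over ρ from 0.3 to 0.8, with half to all dropouts having a 6-month value, power is 78.8% to 83.1%, a gain of 0.4 to 4.7 points.

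**4. Bias if loss depends on 6-month control in one arm.** Further assumptions, none in the article: 6-month mean 8.0% with SD 1.7, base missingness 20% in both arms, and an extra probability e of missingness for intervention patients whose 6-month HbA1c is below 7%. The cut-off is at (7 − 8)/1.7 = −0.588 SD, so 27.8% of patients fall below it and the normal density there is 0.336.

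- Retention in the intervention arm = 0.8 − 0.278e.
- Shift in 6-month HbA1c among those retained = 0.336e / retention, in SD units.
- Approximate bias after baseline adjustment = 1.7 × (0.7 − 0.5 × 0.5) × shift = 0.765 × shift.

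| e | Intervention arm missing | Shift (SD) | Bias, formula | Bias, simulation |
|---|---|---|---|---|
| 0.15 | 24% | 0.066 | +0.05 | +0.05 |
| 0.30 | 28% | 0.141 | +0.11 | +0.11 |
| 0.50 | 34% | 0.254 | +0.19 | +0.20 to +0.21 |

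A positive sign means that the intervention looks worse. If the extra loss falls instead on intervention patients above 9%, the setting is a mirror image and the biases are −0.05, −0.11 and −0.21, so the intervention looks better. If the same extra loss occurs in both arms, the bias is about zero.

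A likelihood estimate that uses the 6-month value has bias below 0.01 in every scenario when all patients have that value. If half the dropouts lack it too, the bias is only partly removed.

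**5. Against the margin.** 0.05/0.4 = 13% and 0.11/0.4 = 27%. The last row reaches about half the margin, but it needs 20 + 50 = 70% missing among well-controlled intervention patients.

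**The case against.** **No complete-case rule is written.** Linear regression is compatible with multiple imputation, including imputation that uses the 6-month value, and such detail usually sits in a SAP or full protocol not shown here. This stands. A reader might infer that the plan drops patients without a 12-month HbA1c; the article does not say so. The single 12-month time point is likewise inferred. What remains is the choice that was published: a named model with no stated role for a measurement already collected.

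**The article has a safeguard.** Discharged patients return to their GP, and GP records are the stated back-up for missing clinical data, so discharge is not the same as loss. This stands too: the loss may be well below 20%, and discharge requires three kinds of target rather than HbA1c alone. But the sizing still allows for 20% attrition, and the article names no method for values still missing after the record search. The best-estimation technique in the Discussion concerns survey items.

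**The discharge mechanism is conservative.** Losing well-controlled intervention patients makes the intervention look worse. A reader might take the half-margin figure as a threat of false non-inferiority. Under this mechanism the opposite holds: a false claim becomes less likely. Only selective loss of poorly controlled intervention patients favours the intervention, and the article neither predicts nor excludes that.

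**The gain is small.** Baseline-adjusted regression is a standard analysis, and 2 to 5% in SE is modest. That is correct; the case rests mainly on bias.

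**Conclusion.** The point holds as an inexpensive improvement to a stated analysis choice, not as an error that invalidates the trial. Read literally, the primary regression leaves the 6-month HbA1c unused and analyses only patients with a 12-month value, which sits badly with the intention-to-treat label when 20% attrition is expected.

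The plausible size is a bias of about 0.05 to 0.1 HbA1c points, or 13 to 27% of the margin. It arises only if loss that remains after the GP record search depends on interim control differently by arm, and its direction depends on which patients are lost. These figures rest on assumed correlations, an assumed 6-month mean of 8.0% and assumed cut-offs of 7% or 9%. The half-margin figure belongs to an extreme scenario and should not be quoted as the expected size.

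**What to change.** Make the primary analysis a mixed model for repeated measures on 6- and 12-month HbA1c. Include all randomised patients with any follow-up value, analysed as randomised, with arm-by-time, baseline HbA1c-by-time, catchment area (the randomisation stratum) and an unstructured covariance. Name the 12-month arm contrast as the primary estimate and compare its confidence interval with the margin.

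Add one sensitivity analysis that imputes missing intervention values as worse by up to the margin. This tests the direction that could produce a false non-inferiority claim. With 20% missing, the full 0.4 penalty moves the intervention mean by 0.2 × 0.4 = 0.08.

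The cost is analysis wording, standard software and slightly more analysis work, with no new visits or data. The model assumes that values are missing at random given arm, the covariates and the observed HbA1c values. It protects only for dropouts who have a 6-month value, so the GP record search should still be pursued equally in both arms.

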## Methods/Design

### Study design

The study uses a non-inferiority randomised controlled trial design. A mixed methods approach of data collection including quantitative and qualitative methods is used. Non-inferiority trials are designed to show that a novel treatment is at least no worse than a standard treatment in terms of some primary clinical endpoint
[25], in this case HbA1c. Accordingly, the primary hypothesis is that glycaemic control of patients with T2DM who have their treatment delivered through management by a community-based multidisciplinary integrated primary-secondary healthcare team (including an Endocrinologist) using protocol driven care, will be comparable to glycaemic control achieved in a hospital outpatient clinic setting.

The research questions include:

1. What is the impact of the new model of care on glycaemic control and other clinical indicators compared to usual care?

2. What is the impact of the new model of care on patient-reported outcomes compared to usual care?

3. What is the cost-effectiveness and cost utility of the new model of care compared to usual care?

4. What are the perspectives and experiences of patients and health professionals regarding the new model of care?

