### Recruitment and randomisation

Research staff located at each participating hospital will contact eligible patients by telephone to introduce the study, confirm eligibility, gain verbal consent for participation and confirm patients’ contact details. Urgent (Category 1) patients will be contacted as a priority so they can be seen within 1 to 2 weeks of referral. Eligible, interested patients will be sent an Introductory Letter, a Participant Information Sheet and a Consent Form. Patients who wish to participate will be asked to sign and return the Consent Form by post or email. Patients who refuse to participate will be treated at the hospital diabetes outpatient clinics.

After consent, each participant will be randomly allocated to the intervention or usual care group, facilitated by an online computerised centralised allocation process. Participants will be randomly assigned to the intervention or usual care group using a computer-generated random number sequence with an allocation ratio of 3:1 intervention to usual care. Randomisation will be conducted remotely and in advance, by the study statistician, who is blinded to the identity of participants. Participants will be stratified by catchment area for randomisation, and then will be randomised to either a community-based complex diabetes services site (intervention) or a hospital site (usual care). Allocation to group will be concealed to the researcher during the recruitment and consenting process. The researcher will access the secure website after the patient has provided written consent to obtain the participant’s group allocation.

Once randomised, patients will be notified of their appointment details by standard practice (that is, letter). The detailed recruitment steps are shown in Figure 
1.

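### The primary regression names no variance estimator; under 3:1 allocation the default pooled standard error is right only if both arms have equal spread, so a robust one should be named

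*Protocol article*

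**What the plan says.** The section Statistical analysis plan of the protocol article states that "The analysis of the primary outcome (HbA1c) will be assessed using linear regression". It adds that "the baseline score of the outcome of interest will be included as a covariate in models" and that "Site allocation will also be included in models as a covariate". On the error rate it says "Statistical significance will be based on two-tailed tests", at the 0.05 level. No standard error is specified, whether ordinary, robust or arm-specific, and no baseline-by-arm term is mentioned.

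The section Sample size and power calculation works from a single spread for both arms: "the sample size calculation used a pooled standard deviation in HbA1c of 1.7"%. It sets a margin of 0.4%, a predicted difference of 0.1%, attrition of 20% in both groups and a total of 456. The section Recruitment and randomisation fixes "an allocation ratio of 3:1 intervention to usual care".

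**The concern.** Ordinary linear regression estimates one residual variance and uses it for both arms. With equal arm sizes this does no harm, because the standard error of the arm difference stays right in large samples even when the spreads differ. With 3:1 allocation that protection is gone. The larger intervention arm dominates the pooled variance, while the smaller usual-care arm dominates the true uncertainty of the difference.

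The non-inferiority decision rests on one confidence limit set against 0.4%, so a misstated standard error acts directly on the conclusion. If usual care is the more variable arm, the limit is too tight and non-inferiority is claimed too often. If usual care is the less variable arm, the limit is too wide and power is lost.

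**Working it through.** **Inputs from the article.** Total 456, attrition 20%, allocation 3:1, pooled SD 1.7%, margin 0.4%, predicted difference 0.1%, two-tailed 0.05 at analysis (2.5% in the non-inferiority direction). **Assumed:** the arm-specific SDs and slopes, and that the 0.1% favours the intervention (the article does not give its direction).

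**The plan's own figure.** Usual-care n = (1 + 1/3) × [1.7 × (1.645 + 0.842) / (0.4 + 0.1)]² = 95.3, a total of 381.2. Rounding to 4 × 95 = 380 and multiplying by 1.2 gives 456. The total therefore reproduces with one common SD, one-sided 0.05, a favourable difference and inflation by 1.2. How that one-sided 0.05 fits with the two-tailed analysis is a separate matter and is not used here.

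**Evaluable patients.** 456 × 0.8 = 364.8, that is 273.6 intervention and 91.2 usual care.

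**Pooled against true standard error.** Write s1 and s0 for the intervention and usual-care SDs, and c = 1/273.6 + 1/91.2 = 0.01462. In large samples:

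- pooled: SE² = (0.75 s1² + 0.25 s0²) × c
- true: SE² = s1²/273.6 + s0²/91.2 = (0.25 s1² + 0.75 s0²) × c

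The two weights are swapped. With r = s0/s1, the ratio pooled SE / true SE is √[(3 + r²)/(1 + 3r²)]. At 1:1 both sets of weights are 0.5 and the ratio is 1 for any r. The actual false non-inferiority rate at the margin is Φ(−1.96 × ratio):

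| r (usual care / intervention) | SE ratio | Actual rate, nominal 2.5% |
|---|---|---|
| 0.8 | 1.117 | 1.4% |
| 0.9 | 1.054 | 1.9% |
| 1.0 | 1.000 | 2.5% |
| 1.1 | 0.953 | 3.1% |
| 1.2 | 0.913 | 3.7% |
| 1.25 | 0.895 | 4.0% |

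The rate does not depend on whether 456 or 365 patients are analysed. If the limit were one-sided at 5%, the range for r from 0.8 to 1.25 would be 3.3% to 7.0%.

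**Two cases that agree with the stated 1.7%.** Both have pooled variance 2.92 (SD 1.71) and pooled SE √(2.92 × 0.01462) = 0.207. Power is at a true 0.1% benefit, before any gain from baseline adjustment.

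- SD 1.6 intervention, 2.0 usual care: 0.75 × 2.56 + 0.25 × 4.00 = 2.92. True SE = √[(0.64 + 3.00) × 0.01462] = 0.231. Rate 4.0%. Apparent power Φ[(0.5 − 1.96 × 0.2066)/0.2307] = 66%; with the correct SE, Φ(0.5/0.2307 − 1.96) = 58%.
- SD 1.8 intervention, 1.4 usual care: 0.75 × 3.24 + 0.25 × 1.96 = 2.92. True SE = √[(0.81 + 1.47) × 0.01462] = 0.183. Rate 1.3%. Power with the pooled SE Φ[(0.5 − 1.96 × 0.2066)/0.1826] = 70%; with the correct SE, Φ(0.5/0.1826 − 1.96) = 78%.

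**Simulation of the baseline-adjusted regression.** 274 and 91 patients, true deficit 0.4%, baseline SD 1.7 (assumed), 20,000 trials per setting, no site covariate:

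| Setting (usual care relative to intervention) | Ordinary SE | HC3 |
|---|---|---|
| Equal SD, equal slopes | 2.5% | 2.5% |
| Residual SD ratio 1.25 | 4.1% | 2.5% |
| Residual SD ratio 0.8 | 1.5% | 2.6% |
| Slopes 0.4 intervention, 0.6 usual care, equal SD | 2.5% | 2.4% |
| Slopes 0.3 intervention, 0.7 usual care, equal SD | 2.8% | 2.5% |
| Slopes 0.7 intervention, 0.3 usual care, equal SD | 2.9% | 2.4% |

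Spread drives the effect and slope alone contributes little. HC3 holds the nominal level throughout.

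**The case against.** The strongest objection is that the article does not commit to the ordinary standard error. It states no equal-variance assumption, and a robust standard error is fully compatible with the words linear regression. The choice of estimator is a detail that an article commonly leaves to the analysis plan, which is not shown. That stands, and it is why this is not called an error. What remains is that the article does fix the model and the 3:1 ratio, and an analyst following the text as written would by default use the one estimator that this ratio makes fragile.

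The second objection is that nothing in the article shows unequal spread. A reader might infer from "using protocol driven care" that the intervention compresses HbA1c, so that usual care is the more variable arm and the error is inflated. The documents do not support that step. They say nothing about spread by arm. Usual care also has an educator visit, specialist assessment and an insulin stabilisation service, while the intervention runs at three sites with several Clinical Fellows and plans that address each patient's own priorities. Either arm could be the more variable, so this objection stands as well.

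**Conclusion.** The point holds as a conditional one that runs in both directions. If the ordinary standard error is used, the nominal 2.5% false non-inferiority rate lies between about 1.4% and about 4.0% for usual-care to intervention SD ratios of 0.8 to 1.25, and is exactly nominal when the SDs are equal. The range rests on assumed SD ratios; the article supplies only the pooled 1.7%.

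Two stronger readings should be resisted. One is that the plan's false-claim rate is 4%: that is one end of the range and needs a usual-care SD about 25% larger. The other is that assuming a common baseline slope is a comparable fault: slopes as far apart as 0.3 and 0.7 bring the rate only to about 2.9%. This is a cheap improvement, not a mistake in the text.

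**What to change.** In the section Statistical analysis plan, add one sentence: the confidence interval for the primary HbA1c comparison will use heteroscedasticity-robust (HC3) standard errors or, equivalently in purpose, residual variances estimated separately by arm. The same sentence can cover the linear models for secondary outcomes. A mean-centred baseline-by-arm term is optional. It keeps the arm coefficient as the average effect and may add a little precision, but it is not needed to control the error rate.

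No new data are required. Under Trial status the article reports 111 of the planned 456 recruited, so the estimator can be fixed before outcomes are compared. The price is about 1 point of power if the arms are equally variable. If usual care is the more variable arm, the interval becomes wider and power lower (58% against an apparent 66% in the example above), which is the honest figure. If usual care is the less variable arm, power is recovered.

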### Study settings

There are five study sites located in the southern area of Brisbane, Australia. The intervention will be administered in three community-based complex diabetes services. Usual care will be delivered at two hospital diabetes outpatient clinics.

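### Site of care, entered as a fixed covariate beside arm, leaves the treatment effect unidentified; the model should name catchment area, the randomisation stratum

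*Protocol article*

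**What the plan says.** All references are to the protocol article.

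- **Model (Statistical analysis plan).** For the primary endpoint: "The analysis of the primary outcome (HbA1c) will be assessed using linear regression". Secondary outcomes use linear or logistic regression according to type. Two adjustments are named for the models in general: "the baseline score of the outcome of interest will be included as a covariate in models", and "Site allocation will also be included in models as a covariate". The section does not define site allocation, give its number of levels or mention a random effect.
- **Sites (Study settings).** "There are five study sites located in the southern area of Brisbane, Australia". Their roles are separate: "The intervention will be administered in three community-based complex diabetes services. Usual care will be delivered at two hospital diabetes outpatient clinics". No site is described as delivering both kinds of care.
- **Randomisation (Recruitment and randomisation).** Individual patients are randomised 3:1, and "Participants will be stratified by catchment area for randomisation". The same paragraph uses the word site for the place a patient is randomised to: a community site is the intervention, a hospital site is usual care.
- **Strata (Inclusion and exclusion criteria).** There are three catchment areas, drawn along the boundaries of the three community services.

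**The concern.** Where a patient is treated is the intervention in this trial. A covariate for place of treatment therefore carries the whole of the treatment contrast and cannot be separated from it. Adjusting for site is routine when every site treats patients in both arms. Here no site does.

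The factor that does contain both arms at each level is catchment area. It is the stated stratification factor, yet the analysis section names a different factor. At stake is whether the primary model, and every secondary model built the same way, returns the randomised comparison of community with hospital care or a coefficient fixed by the software's handling of a redundant column.

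**Working it through.** The article's only calculated figure, the total of 456, plays no part here. The check concerns the structure of the model and needs no value for the SD, the margin or the site sizes.

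**Inputs**
- Five sites: three intervention-only, two usual-care-only (Study settings).
- Three catchment areas, with individual 3:1 randomisation within each (Inclusion and exclusion criteria; Recruitment and randomisation).
- Regression with the baseline value as a covariate and no random effect (Statistical analysis plan).

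**Step 1: site of care beside arm.** Let A = 1 for intervention and 0 for usual care. Let S1, S2, S3 indicate the community sites and S4, S5 the hospitals. Because each site serves one arm,

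A = S1 + S2 + S3, and 1 − A = S4 + S5.

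Take S5 as the reference site. The columns are intercept, A, S1, S2, S3, S4, which makes 6. Since A − S1 − S2 − S3 = 0, the rank is 5. Adding baseline HbA1c gives 7 columns and rank 6, which a numerical check confirmed. A community site as reference does not help, because intercept − A = S4 + S5 is then the redundancy.

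**Step 2: what this does to the treatment coefficient.** At equal baseline, the fitted mean at community site j is b0 + t + gj, and at hospital k it is b0 + gk. Replace t by t + c, and each of g1, g2, g3 by itself minus c. Every fitted mean is unchanged for any c, so the data cannot determine t. The same holds for the linear predictor of a logistic model.

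**Step 3: what software reports.** It removes a redundant column.
- If A is removed, no treatment coefficient is printed.
- If S3 is removed with S5 as reference, site 5 has mean b0 and site 3 has mean b0 + t. The coefficient labelled arm is then community site 3 minus hospital 5, adjusted for baseline.
- Other codings give other pairs. There are 3 × 2 = 6 possible community–hospital pairs, and none is the comparison of all intervention patients with all usual-care patients.

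**Step 4: alternatives.** Rank and estimability were checked on a simulated layout of 364 patients (456 × 0.8 = 364.8), with intercept, arm and baseline in each model. The link between catchments and hospitals was assumed.

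| Added factor | Columns | Rank | Arm estimable |
|---|---|---|---|
| Site of care (5 levels) | 7 | 6 | no |
| Catchment area (3 levels) | 5 | 5 | yes |
| Recruiting hospital (2 levels) | 4 | 4 | yes |

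Catchment area works because each stratum contains patients of both arms.

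**Step 5: cost of the catchment model.** In the same layout, with the residual SD held at 1.7, the standard error of the arm effect is 0.214 with catchment adjustment and 0.211 unadjusted. The layout did not force balance within catchments and assumed no catchment effect on HbA1c. It shows that the adjustment costs almost nothing; it does not show a gain.

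**Step 6: fewer sites.** The Trial status section reports four sites engaged so far. With four single-arm sites, both arms represented and baseline included, there are 6 columns and rank 5. The fault is the same.

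**The case against.** The strongest reply is that the failing model is inferred. The article never defines site allocation, never says it has five levels, and lists no separate arm term. Three other readings leave the effect estimable:

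- **Catchment area.** Catchments follow the community services' boundaries, so site could be shorthand for the stratum. The fix would then be what was already meant.
- **Recruiting hospital.** Patients are recruited through two hospitals before randomisation, and that factor is crossed with arm.
- **The arm itself.** Randomisation is described as being to one type of site or the other, so site allocation could be the treatment term, loosely called a covariate.

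All three are possible, and the article excludes none of them. They do not rescue the sentence as written. The randomisation section uses a different term for the stratum and keeps site for the place of assigned care, so site of care is the plain reading. On the other readings the wording needs correction, and catchment area is named in the model only if site was shorthand for it.

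It can also be said that a model with site indicators and no arm term has full rank and allows an estimable contrast: the mean of the three community sites minus the mean of the two hospitals. That is correct, but the article specifies neither that contrast nor its weights.

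A reader might go further and infer three things that the documents do not support:
- *The trial cannot estimate its treatment effect.* The design allows it. Only one reading of one sentence prevents it.
- *The fault has a calculable cost in precision against the 0.4% margin.* Any such figure would rest on site sizes the article does not give and on which column happens to be dropped.
- *Leaving out catchment area loses precision.* The article reports no effect of catchment on HbA1c.

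Finally, the article is condensed, and covariate definitions are often left to a full analysis plan. That would excuse silence. Here the article states a rule that fails when followed literally.

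**Conclusion.** The point holds in a conditional form. If site allocation means site of care, entered as a fixed factor alongside arm, the treatment coefficient is not identified in the primary model or in any secondary model of the same form (rank 6 of 7 with baseline included). This is exact. It rests only on each site serving one arm, which Study settings and Recruitment and randomisation both support. If catchment area, recruiting hospital or the arm itself was meant, the effect is estimable and the fault is one of wording.

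On every reading the sentence needs correcting before the primary analysis, because it defines the primary model and does not name the factor by which patients were stratified. The case for catchment area is identifiability and consistency with the randomisation, not power.

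**What to change.** Replace the sentence on site allocation in the Statistical analysis plan section with:

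*Catchment area (the randomisation stratum, three levels) will be included as a covariate; site of care will not be entered as a fixed effect alongside treatment arm.*

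If a full analysis plan exists, it should carry the same definition. Showing results by site descriptively is optional and is not needed to cure the fault.

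The cost is one sentence. Catchment area is already needed for eligibility and for stratified randomisation, so no new data are required, and the sample size does not change.
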